### Secondary analysis to facilitate interpretation of the primary outcome

a) Developing a non-linear model of early head growth (if data analysis indicates this is required)

b) Longitudinal joint modelling of head growth and survival;

c) Longitudinal joint modelling of head growth and protein/calorie intake

d) per protocol analysis omitting babies that received PN other than that due under their allocation for more than 24 hours;

e) exploratory data analysis of how potential confounding variables are distributed between the two intervention groups

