## Methods/Design

### Trial design

A single centre, parallel group, randomised controlled trial with blinding of parents and outcome assessors. The control group will receive the standardised, concentrated neonatal parenteral nutrition formulation (scNPN) used in current clinical practice and the intervention group will receive a similar formulation containing additional macronutrients (scNPN_max_).

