### Subject withdrawal

Patients may be withdrawn if the parent(s)/guardian(s) withdraws consent. Following withdrawal patients will be managed according to usual clinical practice. This means the patient will receive scNPN and routine biochemical and growth monitoring. Parents will be asked whether or not they consent to trial-related data to be collected for their baby(ies) and whether or not they consent to the continued use of information that has already been collected about their child.

Occasionally, infants on PN can become metabolically unstable (as determined by routine biochemical monitoring). This is usually managed by stopping or reducing PN and then gradually reintroducing PN once things improve. If such improvement is not sustained then an independent clinician and biochemist will discuss the need for possible withdrawal from the trial.

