### Administration

The administration of scNPN (or scNPN_max_) will follow the current LWH NICU PN administration guidelines and will not differ from PN administration in infants not in the study (these infants will all receive scNPN). Following birth, scNPN will be administered until consent is obtained and the patient randomised to receive either scNPN or scNPN_max_. In accordance with the PN guidelines, PN administration will continue until the child is on 75% enteral feeds. If enteral feeds are stopped or markedly reduced (<25% total intake) after this point and the infant is <28 days, the original study PN will be restarted as soon as practical. If feeds are reduced but still exceed 25% total, study PN will be reintroduced only if enteral feeding <75% persists for more than 24 hours. All infants who need PN after 28 days will be prescribed scNPN. The introduction of PN, PN infusion rates (including the management of supplementary infusions) and reduction of PN with increased enteral feeds are described in detail in LWH NICU PN guidelines.

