### Assessment of compliance with study PN

The amount prescribed is not necessarily the amount that a baby receives. Effectiveness of PN delivery is a secondary outcome for this study. Detailed and comprehensive information about the amount of PN infused is collected in the medical record. This will be transcribed to the CRF. This will allow accurate calculation of actual daily PN administration to individual patients. The results of these calculations will be recorded on the CRF. Expected daily PN is also recorded in the medical record. This will allow identification of any major deviation (>15 ml/kg/day) from the LWH guidelines. Non-trial PN will be administered until the infant is randomised. Following randomisation, administration of the non-trial PN/fluids may occasionally occur (eg severe hypoglycaemia, transfer to operating theatre or another centre). Administration of non-trial PN/fluids will still be fully recorded to allow full nutritional for the first 28 days to be calculated.

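### Per-protocol item d is structurally asymmetric: reverting to unit PN breaches it in the scNPNmax arm but not in the control arm, so exclusions can be differential

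*Protocol article*

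**What the plan says.** Item d of the protocol article's section on secondary analyses that support the primary outcome specifies a "per protocol analysis omitting babies that received PN other than that due under their allocation for more than 24 hours". It compares the PN received with the PN allocated, and it states no time window.

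Four statements elsewhere show which PN an infant gets when it is not on study PN:

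- Trial design: "The control group will receive the standardised, concentrated neonatal parenteral nutrition formulation (scNPN) used in current clinical practice".
- Administration, on infants outside the study: "these infants will all receive scNPN".
- Administration, on the time before randomisation: "Following birth, scNPN will be administered until consent is obtained".
- Subject withdrawal, on management afterwards: "This means the patient will receive scNPN and routine biochemical and growth monitoring".

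Subject withdrawal also covers metabolic instability. The first response is a change of amount: "This is usually managed by stopping or reducing PN and then gradually reintroducing PN once things improve". Withdrawal comes later: "If such improvement is not sustained then an independent clinician and biochemist will discuss the need for possible withdrawal from the trial".

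The primary analysis is by intention to treat in survivors.

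**The concern.** scNPN has three roles: control treatment, unit default and PN after withdrawal. A rule that asks whether an infant received something other than its allocated product cannot register a control infant's return to unit PN, because the product does not change. It does register the same event in a scNPNmax infant once it has lasted more than 24 hours.

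One in-house route off study PN is withdrawal after metabolic instability that does not settle. Infants who take that route may well grow more slowly than the others. If so, item d removes slow growers from scNPNmax and leaves their counterparts in control. The per-protocol contrast then moves towards the intervention for a reason unrelated to its effect. Item d is meant to help readers interpret the primary result, so a per-protocol estimate larger than the intention-to-treat estimate could be misread as a stronger effect under adherence.

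**Working it through.** **The plan's own figure.** The Sample size section gives 75 per group, 80% survival, a 6 mm difference, SD 12 mm, two-sided 0.05 and 80% power.

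- Evaluable per group: 75 × 0.80 = 60.
- Standard error: 12 × √(2/60) = 2.19 mm.
- Power: Φ(6/2.19 − 1.96) = 78.2% by the normal approximation, or 77.5% by the exact t-test.

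This is close to the stated 80%. It does not bear on item d, but it supplies the SD, the group size and the target for the check below.

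**How the rule acts on the same event in each arm.**

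| Event after randomisation, lasting more than 24 h | scNPNmax infant | Control infant |
|---|---|---|
| Withdrawn, then given unit scNPN | omitted | kept |
| Given unit scNPN for another reason | omitted | kept |
| Given a different PN, for example at another centre | omitted | omitted |
| PN stopped or reduced, then resumed | not clearly a breach | not clearly a breach |

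The asymmetry lies in the first two rows.

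**Size under no treatment effect.** Let p and q be the shares omitted from scNPNmax and control, and g the growth deficit (mm over 28 days) of omitted infants relative to those kept. If both arms have the same overall mean m, the retained means are m + p·g and m + q·g, so

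bias = (p − q) × g, with SE = 12 × √[1/(60(1 − p)) + 1/(60(1 − q))].

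The article gives none of p, q or g. All values below are assumptions.

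| p | q | g (mm) | bias (mm) | two-sided type I error |
|---|---|---|---|---|
| 5% | 0 | 3 | 0.15 | 5.1% |
| 5% | 0 | 6 | 0.3 | 5.2% |
| 10% | 0 | 6 | 0.6 | 5.8% |
| 15% | 0 | 8 | 1.2 | about 8% |
| 20% | 0 | 6 | 1.2 | 8.1% |
| 20% | 0 | 12 | 2.4 | 17.8% |
| 20% | 10% | 6 | 0.6 | 5.7% |
| 20% | 20% | 6 | 0 | 5.0% |

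Worked case, p = 15%, q = 0, g = 8:

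- Bias: 0.15 × 8 = 1.2 mm, and 1.2/6 = 20% of the target.
- Kept: 60 × 0.85 = 51 against 60.
- SE: 12 × √(1/51 + 1/60) = 2.29 mm.

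For p = 10%, q = 0, g = 6, the bias is 0.10 × 6 = 0.6 mm, or 10% of the target, with SE 12 × √(1/54 + 1/60) = 2.25 mm. A negative g reverses the sign.

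**The case against.** The case against has real weight, and most of it limits how far the point goes.

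- A reader might infer that exclusions will come almost only from scNPNmax. The article does not show this. Assessment of compliance with study PN calls non-trial PN or fluids occasional and names transfer to another centre among the causes. PN given there is not shown to be scNPN, so control infants can be excluded too.
- A reader might infer that the infants who revert are the sickest. The usual response to instability is to stop or reduce PN, which is not a change of product; withdrawal is only discussed if improvement does not last. Parental withdrawal need not relate to growth at all. On the other side, the Background says the glucose and lipid rates needed may not be tolerated, especially in the first week, and the Blinding section says prescribers can recognise the allocation. More reversion in the richer arm is therefore plausible, but it is not established.
- A reader might infer that item d could turn a null trial into a positive one. At the assumed 15% and 8 mm, the bias is about half a standard error and the type I error is about 8%. The primary analysis is not touched, and item c already models head growth jointly with protein and calorie intake.
- Because scNPN is given before randomisation, a literal reading might breach the rule in most scNPNmax infants. That does not hold: before randomisation no PN is due under an allocation. The unstated window is only a reason to write it down.
- A reader might see a second uneven rule in the volume threshold for compliance: "This will allow identification of any major deviation (>15 ml/kg/day) from the LWH guidelines". The article ties that flag to no exclusion, so it adds nothing here.

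What survives is the asymmetry itself. No other statement in the article removes it. The Analysis section defers the handling of missing data to a later plan, whereas item d already fixes this exclusion rule.

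**Conclusion.** The point holds in a limited form. As worded, item d treats more than 24 hours on unit PN as a breach in the scNPNmax arm and not in the control arm. It can therefore exclude infants differentially from scNPNmax and, if those infants grow less, favour the intervention. That the analysis will be biased, and in which direction, cannot be concluded from the article, because both depend on unstated exclusion rates and on the growth of the excluded infants. With no control exclusions and assumed values of 5 to 20% excluded and a 3 to 12 mm deficit, the bias runs from 0.15 to 2.4 mm against the 6 mm target; 0.6 to 1.2 mm is a reasonable illustration. It shrinks to zero as control exclusions come to match in rate and prognosis. The consequence is confined to one supportive analysis.

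**What to change.** Reword item d so that the deviation is an event that can occur in either arm: withdrawal from, or reversion off, study-allocated PN for more than 24 hours between randomisation and day 28, whichever product is then given. A control infant withdrawn to unit scNPN is then omitted on the same terms as a scNPNmax infant. Report exclusions by arm and reason, because an even definition does not guarantee even rates.

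Alternatively, replace item d with a complier-type (instrumental variable) estimate, with allocation as the instrument and receipt of the allocated regimen as the exposure. This drops nobody. Protein intake alone should not be the exposure, because Table 1 shows that allocation also changes lipid, glucose and calories. Infants who received part of the regimen before reverting need a stated convention.

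A common cut on the percentage of expected macronutrient delivered is not a good substitute: if the richer regimen is less well tolerated, that arm could fail the cut more often, again among sicker infants.

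The cost is slightly more analysis work and, under the first option, a few more control exclusions. The protocol already records non-trial PN and fluids in full and has the pharmacies track allocation of trial materials, so treatment and routine data collection need not change.

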### Secondary analysis to characterise the trial

Exploratory data analysis will be used to describe the relationships between treatment allocation and:

a) growth measures expected to be concordant with the primary outcomes

b) efficiency of nutrient delivery

c) metabolic tolerance to each regimen

d) issues relating to the delivery of the nutritional regimens

e) major neonatal morbidity

f) neurodevelopmental outcome at 2 years

## Discussion

### Safety and adverse event reporting

Adverse events are relatively common in this patient group due to immaturity and to concomitant disease processes. Randomisation is essential for a comparison of safety among those receiving a study intervention compared to an appropriate comparator group. Routine clinical monitoring will be used to ensure that biochemical monitoring stays within limits defined within LWH clinical guidelines. Glucose and triglyceride monitoring have guidelines in place to allow PN to be adapted if abnormal levels arise. Abnormal amino acid profiles are discussed with a biochemist. These levels of PN macronutrients have been used in several previous studies without safety concerns.

Expected SAEs (Table 3) that are often observed during the course of care following birth at less than 30 weeks gestation before 36 PCA will be recorded on the specific CRF. All deaths or suspected overdoses will be reported to the Sponsor by the Chief Investigator within 24 hours using the SAE report form. All SAEs and deaths will be reported to and reviewed by the Sponsor and DMC at regular intervals throughout the trial. In order to examine whether the pattern of these events differs between the treatment groups, the incidence of these adverse events will be tabulated and presented to the DMC at intervals defined in the DMC Charter. Potential suspected unexpected serious adverse reactions (SUSARs) will be reported to the R & D department at LWH within 24 hours of the investigator becoming aware of them. The R&D Department will evaluate reported events according to severity, causality and expectedness according to the Sponsor's Standard Operating Procedures. SUSARs will be reported to MHRA/LREC within the statutory time-frames

**Table 3 T3:** List of Expected Serious Adverse Events

Serious adverse event	**Estimated incidence **[17]
Death	20%
Necrotising enterocolitis (diagnostic radiological/surgical changes)	15%
Intracranial abnormality on cranial ultrasound scan	15%
(paraenchymal haemorrhage or focal white matter injury)	
Ventilator dependency (28 days) and/or oxygen dependency (36 weeks CGA)	65%
Patent ductus arteriosus medical or surgical management	25%
Retinal surgery for retinopathy of prematurity	5%
Pulmonary haemorrhage	5%
Infection ( positive blood culture with clinical signs)	65%
Persistent derangement of liver function tests (36 wks CGA)	10%
Serious extravasation injury (permanent scarring and/or/joint deformity)	<5%

CGA: corrected gestational age

### Trial Oversight

#### Data Monitoring and Ethics Committee (DMEC)

An independent Data Monitoring and Ethics Committee (DMEC) has been formed. During the period of recruitment, interim summaries of mortality and SAE will be supplied, in the strictest confidence, to the DMEC by the trial statistician. The DMEC has confirmed its terms of reference and frequency of meetings (approximately 6 monthly, depending on recruitment rate) in its first meeting, before the trial began. In the light of interim data and emerging evidence from other studies, the DMEC will inform the Trial Steering Committee if, in their view, there is proof beyond reasonable doubt that the data indicate that any part of the protocol is indicated or contraindicated either for all infants or for a particular subgroup of trial participants.

#### Trial Steering Committee (TSC)

A Trial Steering Committee has been formed to supervise the conduct of the study. The terms of reference were agreed in its first meeting (before the trial began). The TSC will meet (minimum frequency) within a month of all DMC meetings to consider their recommendations.

#### Study Timetable

Recruitment started in October 2009 following final protocol approval by ethics committee and the Medicines and Healthcare products Regulatory Agency (MHRA). It is anticipated recruitment will have completed in April 2012 allowing analysis of the primary outcome to be completed by December 2012. The last neurodevelopmental assessment would be completed in August 2014.
